### Quality

Sonographers will be trained to perform first trimester 3D VR ultrasound scans. As the first trimester ultrasound scan for fetal anomalies is currently not part of standard care in the Netherlands, the sonographers will receive additional training. They will all collect a portfolio comprising 5 complete ultrasound examinations, which will be reviewed by two experts. Unsatisfactory portfolios will be discussed with the sonographers in order to improve quality. When at least 5 high quality examinations of different patients have been collected, the sonographer can participate in the study.

To ensure quality of the first trimester ultrasound, all sonographers are asked to compile a new portfolio every 200 first trimester ultrasound scans.

### Statistical issues

#### Sample size

The prevalence of anomalies in the high risk group is 5–10% [38, 39]. The detection rate for fetal anomalies with 2D ultrasound in the first trimester lies between 18.2 and 71.8% [7]. As mentioned before, the detection rate in a high risk population is estimated at 61%, and in a low risk population at 63% for 2D ultrasonography [6, 8]. The detection rate for anomalies of the first trimester 3D VR ultrasound is 62.5% [20]. For second trimester (18–22 weeks’ gestation) 2D ultrasound the detection rate lies between 44.3 and 74.4% [40–42].

For sample size calculation with a superiority analysis we assumed a 65% detection rate for a second trimester 2D ultrasound examination and a 70% detection rate for the combined detection of first trimester 3D VR and second trimester 2D ultrasound examination in a high risk population. With an assumed prevalence of 7.5% and an alpha-error of 0.05 with a desired power of 0.80, a total group of *N* = 2800 is required.

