**Methods:**

Women in the first trimester of a high risk pregnancy for a fetus with a congenital anomaly are eligible for inclusion. This is a randomized controlled trial with two intervention arms. The control group receives ‘care as usual’: a second trimester 2D advanced ultrasound examination. The intervention group will undergo an additional first trimester 2D and 3D VR ultrasound examination. Following each examination participants will fill in validated questionnaires evaluating their quality of life and healthcare related expenses. Participants’ and ultrasonographers’ perspectives on the 3D VR ultrasound will be surveyed. The primary outcome will be the detection of fetal anomalies. The additional first trimester 3D VR ultrasound examination will be compared to ‘care as usual’. Neonatal or histopathological examinations are considered the gold standard for the detection of congenital anomalies. To reach statistical significance and 80% power with a detection rate of 65% for second trimester ultrasound examination and 70% for the combined detection of first trimester 3D VR and second trimester ultrasound examination, a sample size of 2800 participants is needed.

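### The 2,800 participants do not follow from the stated inputs: the figure matches the number of affected fetuses needed, and as a participant count it gives about 12% power, not 80%

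*Protocol article*

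**What the plan says.** The Sample size section of the protocol article sets up a superiority comparison. For the control arm, "we assumed a 65% detection rate for a second trimester 2D ultrasound examination". For the intervention arm it takes "a 70% detection rate for the combined detection of first trimester 3D VR and second trimester 2D ultrasound examination". It then concludes: "With an assumed prevalence of 7.5% and an alpha-error of 0.05 with a desired power of 0.80, a total group of" 2,800 is needed. The Methods part of the abstract fixes the unit: "a sample size of 2800 participants is needed".

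The same section gives a range for the prevalence: "The prevalence of anomalies in the high risk group is 5–10" per cent.

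Outcome measurements makes the detection rate the primary outcome, with neonatal or histopathological examination as the reference standard, and lists sensitivity as the first of its measures. Study design puts the two strategies in separate randomised arms. The Discussion confirms that the contrast of interest is first plus second trimester scanning against second trimester scanning alone.

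**The concern.** Sensitivity can be estimated only in fetuses that have an anomaly. At a prevalence of 7.5%, more than nine in ten participants contribute nothing to the primary comparison. A 5-point difference around 65% to 70% is small and needs well over a thousand affected fetuses per arm, so a total of 2,800 participants looks far too low.

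What is at stake is how the main result will be read. If the trial is believed to have 80% power, a non-significant difference will be taken as evidence that the early scan adds nothing to detection. The Discussion says the results should inform policy on adding this scan to routine care. If power is in fact very low, a non-significant result is the likely outcome even when the assumed benefit is real.

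**Working it through.** **Inputs.** From Sample size: p1 = 0.65, p2 = 0.70, prevalence 0.075 (range 0.05 to 0.10), alpha 0.05, power 0.80, total 2,800. Assumed because not stated: two-sided test, 1:1 allocation, one fetus per participant, no loss to follow-up.

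**Step 1. Reproduce 2,800.** Two independent proportions, pooled variance under the null, mean proportion 0.675:

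n per arm = [1.960 × √(2 × 0.675 × 0.325) + 0.842 × √(0.65 × 0.35 + 0.70 × 0.30)]² / 0.05²

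= [1.960 × 0.6624 + 0.842 × 0.6614]² / 0.0025 = 1,376.3, rounded up to 1,377.

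The total is 2,754. Variants give 2,747 (unpooled), 2,751 (arcsine) and 2,834 (continuity-corrected). All lie within about 2% of 2,800, and all count affected fetuses. With 1,400 affected per arm, power is 80.7%. The printed figure is therefore recovered only when prevalence is left out.

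**Step 2. Apply the prevalence.** Participants needed = 2,754 / prevalence:

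| Prevalence | Participants needed |
|---|---|
| 5% | 55,080 |
| 7.5% | 36,720 |
| 10% | 27,540 |

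**Step 3. What 2,800 participants provide.** 2,800 × 0.075 = 210 affected, 105 per arm.

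- Standard error under the null: √(2 × 0.675 × 0.325 / 105) = 0.0646
- Standard error under the alternative: √((0.65 × 0.35 + 0.70 × 0.30) / 105) = 0.0645
- Power, upper tail: Φ((0.05 − 1.960 × 0.0646) / 0.0645) = 0.117; with both tails, 0.120
- Exact binomial calculation: 0.120 for the chi-square test, 0.093 for Fisher's test

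| Prevalence | Affected per arm | Power, 65% vs 70% | Intervention rate detectable with 80% power |
|---|---|---|---|
| 5% | 70 | 9.6% | 85.3% |
| 7.5% | 105 | 12.0% | 82.0% |
| 10% | 140 | 14.5% | 79.9% |

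The power column counts both tails; the upper tail alone gives 9.2%, 11.7% and 14.3%.

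**Step 4. Precision at 105 per arm.** The 95% confidence interval half-width is 1.960 × 0.0645, about 12.7 points, against an assumed effect of 5. The chance that the intervention arm shows the lower observed rate although it is truly 5 points better is Φ(−0.05 / 0.0645), about 22%.

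**Step 5. Other readings of the calculation.**

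| Reading | Result |
|---|---|
| One-sided alpha 0.05 | 2,168 affected, about 28,900 participants; 19% power at 105 per arm |
| 2,800 per arm | 210 affected per arm; 19% power |
| Detected anomalies per participant (4.875% vs 5.25%) | about 107,300 participants |
| One-sample test against 65% | 698 affected, about 9,300 participants in that arm |
| Paired, most favourable (5% vs 0% discordant) | 155 affected, about 2,061 participants all having both strategies |

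None of these gives 2,800 participants for a between-arm comparison.

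**The case against.** The article prints no formula, sidedness or allocation ratio, and it condenses a fuller protocol that is not at hand. That prevalence was left out is an inference from a close but inexact match. Another origin is conceivable: 2,800 × 0.075 = 210, and a paired test of a 5-point difference needs about 210 affected fetuses if roughly 6.8% of them are discordant. Outcome measurements does include comparisons within the intervention arm. Twins are eligible, and one fetus may carry several anomalies, so the denominators could exceed 105. The trial also has quality-of-life and cost objectives that this calculation does not touch.

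Some of this stands. How the figure arose is inferred, and two-sided alpha and 1:1 allocation must be labelled as assumptions. None of it restores 80% power:

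- A paired calculation is not the comparison described in the abstract and the Discussion. The control arm has no first trimester anomaly scan, and the intervention arm would hold only about 105 affected fetuses, fewer than the 155 needed even in the most favourable paired case. The Intervention group section also specifies the routine second trimester scan for women without a first trimester finding, so full pairing is doubtful.
- Doubling the denominators to 210 per arm, well beyond what twins could plausibly add, gives 19% power.
- A fuller protocol might explain the slip, but the article prints both the inputs and a result that they do not produce.

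**Conclusion.** The concern holds. On the protocol's own inputs, 2,800 participants give about 105 affected fetuses per arm and about 12% power for 65% against 70%, with roughly 10% to 14% over the stated prevalence range and about 19% if the test is one-sided. If the assumed benefit is real, about 88% of such trials would be non-significant. The smallest difference detectable with 80% power is about 17 points at 7.5% prevalence, or about 15 to 20 points over the range from 10% down to 5%. The number of participants is short by a factor of about 13 (36,720 / 2,800).

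The shortfall follows directly from the stated inputs under 1:1 allocation and about one affected fetus per affected pregnancy. Only the explanation, that prevalence was named but not applied, is inferred. The error affects the basis of the primary comparison and must be corrected. It does not bear on the quality-of-life or cost analyses.

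**What to change.** Correct the Sample size section and the Methods part of the abstract together:

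- State that 2,800 participants are expected to yield about 210 affected fetuses, 105 per arm, at 7.5% prevalence, with the range for 5% to 10%.
- State the power for 65% against 70% (about 12%) and the difference detectable with 80% power (about 17 points), naming the test, its sidedness and the allocation ratio.
- Delete the claim that 2,800 participants give 80% power.
- Present the between-arm difference in detection rate as an estimate with a 95% confidence interval, and say in advance that a non-significant result does not show absence of benefit.

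This costs wording only and needs no extra participants; the price is a much less favourable stated power. Keeping the 5-point target at 80% power would instead need about 36,700 participants. If the sponsor prefers to power the trial for a larger difference, that difference needs its own justification.

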#### Data-analysis

Data will be analyzed according to the intention-to-treat principle. No interim analysis will be performed.

Statistical analysis will be performed using IBM SPSS (SPSS Inc., Chicago, IL, USA) and R Studio (The R Foundation for Statistical Computing). Descriptive statistics will be used to describe the baseline characteristics of both the control and intervention group (e.g. maternal characteristics such as ethnicity, age, smoking status, Body-Mass Index (BMI) and family history, pregnancy characteristics such as parity and pregnancy outcome, medication use such as antidepressants and antiepileptic medication). Categorical data will be presented by number of participants (%) and numerical data by median (interquartile range). These baseline characteristics will be compared between the arms using Mann Whitney U-test for continuous variables and chi-squared test for categorical variables. When the expected count in 20% or more of the cells of the cross table for the categorical variables is 5 or lower or if any cell is empty an exact test will be used instead. A significance level (alpha) of 0.05 will be used. No multiplicity correction will be applied.

The economic analysis will be performed from the societal perspective. The costs and quality of life will be compared between the two diagnostic regimens. Descriptive statistics will be used to describe the outcomes of quality of life analysis (control arm versus intervention arm).

Ultrasound is considered safe in pregnancy, therefore a data monitoring committee is not required [43]. Yearly reports will be sent to the ethics committee on the progress of the trial. When major modifications to the protocol are made, all people involved will be informed.

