Secondary outcome measures will be health-related quality of life and cost-effectiveness of first trimester 3D VR ultrasound from a societal perspective. Health related quality of life will be expressed in physical, emotional and social functioning. Quality Adjusted Life Years (QALY’s) will be calculated from a maternal perspective, derived from the validated questionnaires. Actual expenses during the study will be measured using the standard costs as stated by the Dutch costing guidelines [37]. For each strategy (control versus intervention) the quality of life will be computed as well as the average costs per patient. The incremental cost-effectiveness ratio (ICER) will be calculated by dividing the difference in costs by the difference in quality of life. It represents the extra costs required to obtain one QALY. Furthermore, the cost per anomaly detected will be estimated. The cost-effectiveness analysis will span a period from approximately 8 weeks of gestation, when regular obstetric care starts, up to approximately 2 months beyond the estimated date of delivery. In this analysis, costs and effects will not be discounted due to a short time frame. Indirect costs will not be accounted for. The costs will be presented in Euros. The index year will be 2018.

Additionally, through a newly implemented questionnaire, the perspective of both patient and ultrasonographers on the new 3D VR modality will be surveyed. The participant perspective of the first trimester 3D VR ultrasound group (=intervention) will be compared to second trimester 2D ultrasound (=control).

An overview of all patients’ characteristics and data is shown in Table 1.

**Table 1 Tab1:** Patient characteristics collected within the VR FETUS study. Details of data collection form the first trimester up to 6 weeks after delivery are depicted

**Maternal Characteristics**	**Outcome**
Age	Years (mean ± SD)
Ethnicity	Dutch/Other western/Non-western
Level of education	Low, middle, high
Postal code	
Medical history	Unremarkable/Diabetes/Epilepsy/Other
Obstetrical history	Parity, miscarriage, previous pregnancy with congenital anomaly
Family history	Unremarkable/family members with congenital anomaly
Marital status	Married/not married
Global household income	€0–20.000/€20.000–35.000/€35.000–65.000/>€65.000 annually
BMI	Kg/m^2^ (mean ± SD)
Alcohol use during first trimester	No/Yes: how many units per day?
Smoking during first trimester	No/yes: how many cigarettes per day

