Recreational drug use during first trimester	No/yes: what drugs; frequency per day?
Folic acid use during and/or prior to pregnancy	No/yes during pregnancy/yes started prior to pregnancy
Pregnant after artificial reproductive technology	No/yes: what type of assisted reproduction
First trimester screening for aneuploidy	No/yes: result
Medication	No/yes: what medication, dosage, starting and stopping date?
Antidepressant	Never/yes currently/yes previous use
**Questionnaires**	**Timing**
Current health status^a^	At inclusion, intervention or 13 weeks’ GA, 20 weeks’ GA, 6 weeks after due date
Anxiety and depression^b^	At inclusion, intervention or 13 weeks’ GA, 20 weeks’ GA, 6 weeks after due date
State and trait anxiety^c^	At inclusion, intervention or 13 weeks’ GA, 20 weeks’ GA, 6 weeks after due date
Current health status by VAS^d^	At inclusion, intervention or 13 weeks’ GA, 20 weeks’ GA, 6 weeks after due date
Medical consumption^e^	At 20 weeks’ GA, 32 weeks’ GA, 6 weeks after due date
Patient satisfaction with 3D VR	At intervention or 13 weeks’ GA, 6 weeks after due date
**Ultrasound**	**Measurements**
At inclusion, 1st trimester	Viability, CRL, multiple pregnancies, location
Intervention: 2D + 3D VR First Trimester Ultrasound, 1st trimester	Fetal anomaly scan using 2D and 3D VR. Growth parameters, detection of anomaly. See supplement A
Advanced fetal anomaly scan, 2nd trimester	Fetal anomaly scan using 2D. Growth parameters, detection of anomaly
**Pregnancy outcome**	**Outcome**
Outcome	Live birth, termination, intra-uterine fetal demise
Mode of delivery	Vaginal / Instrumental delivery / Cesarean section
Gestational age at delivery	Days (mean ± SD)
Invasive testing	No/yes: result
Date of invasive testing	
**Neonatal outcome**	**Outcome**
Birthweight	Birthweight, grams (mean ± SD)
Gender	Male/female
Congenital malformation	No/yes: what malformation
Prenatal diagnosis	Confirmed/discrepancy in findings: postnatal new or other findings

^a^SF-36: MOS 36-item Short Form Health Survey, ^b^HADS: Hospital Anxiety and Depression Scale, ^c^STAI: Spielberger State-Trait Anxiety Inventory, ^d^VAS: visual analogue scale, ^e^iMTA MCQ: iMTA Medical Consumption Questionnaire, CRL: Crown-Rump Length, 2D: two-dimensional, 3D VR: three-dimensional virtual reality

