## Discussion

This is the first randomized controlled trial designed to detect anomalies in the first trimester using 3D VR ultrasonography, with longitudinal follow-up in pregnancy. One previous study has shown a high sensitivity for the detection of structural anomalies in the first trimester using 3D VR and a trend towards improved detection rates [16]. 3D VR may especially improve the detection of surface anomalies in the first trimester [20]. Timely detection of major congenital malformations will provide women at risk with additional time to perform (genetic) testing as well as more time to consider continuation or termination of pregnancy. In current Dutch practice even women from the high risk population are only offered a second trimester anomaly scan. In the high risk group an additional first trimester ultrasound examination may be beneficial since there will be an increased prevalence of anomalies. Furthermore, the absence of a major anomaly following a first trimester 3D VR ultrasound examination could offer earlier reassurance and reduce anxiety in pregnant women. Overall, we hypothesize this will improve cost-effectiveness and patient quality of life.

This study has several strengths. The use of a standardized examination protocol will improve the detection of fetal anomalies. Recent studies have shown increased detection rate of anomalies when a standardized ultrasound protocol is used compared to a strategy that consists of a global fetal survey [6]. Also, transvaginal ultrasound or the combination of transvaginal and transabdominal ultrasound may increase the detection of anomalies in the first trimester compared to only using a transabdominal approach. This is especially true in case of maternal obesity. Detection of anomalies will be further improved by the limited filtering of the ultrasound data by the 3D VR system, which can enhance fetal surface details and thus improve the examination of limbs and face. This technique also provides recognizable and identifiable ‘holograms’ for the future parents.

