Some challenges remain. The introduction of a first trimester ultrasound examination will necessitate an additional prenatal visit, as well as expertise and training of staff. This might increase healthcare costs. This study will add new understanding on maternal psychological functioning throughout pregnancy in relation to prenatal ultrasound. Ideally, we would use structured interviews. However, due to the size of the study this was not a possibility. Instead we chose to use validated questionnaires to investigate maternal stress and anxiety.

Some organ systems are not yet fully developed in the first trimester or are too small to be visualized in detail. As an example, one can state that it is not possible to detect all or a large proportion of fetal cardiac and brain anomalies in early pregnancy. Therefore, second trimester ultrasound examination cannot be omitted, and has to be used in addition to first trimester ultrasound.

From a clinician’s point of view, the first trimester ultrasound should be studied regarding its additional value of diagnostic performance. Rather than comparing first and second trimester ultrasound examination, the performance should be based on the combination of first and second trimester. We expect that first trimester detection will show an improvement in the clinical care of participants and lead to significant improvement in their quality of life. Furthermore, a second trimester ultrasound examination will show the development of a congenital anomaly over time. Parents’ decision for continuation of the pregnancy is likely to be affected by this. The second trimester ultrasound is indispensable, therefore we will study the combined first and second trimester ultrasound examination compared to the second trimester only.

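### Pregnancy outcome, known only after randomisation, is listed as a baseline characteristic and tested between arms as one

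*Protocol article*

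**What the plan says.** The Data-analysis section opens its description of baseline data with "Descriptive statistics will be used to describe the baseline characteristics of both the control and intervention group". The examples in brackets cover maternal characteristics, medication use and "pregnancy characteristics such as parity and pregnancy outcome". It continues: "These baseline characteristics will be compared between the arms using Mann Whitney U-test for continuous variables and chi-squared test for categorical variables", with an exact test where expected counts are small. The level is given as "A significance level (alpha) of 0.05 will be used. No multiplicity correction will be applied".

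Table 1, under Outcome measurements, has its own block headed Pregnancy outcome. It sits apart from the maternal characteristics and also holds mode of delivery and gestational age at delivery. Its first row is coded "Live birth, termination, intra-uterine fetal demise". Earlier pregnancies are recorded elsewhere, under obstetrical history: "Parity, miscarriage, previous pregnancy with congenital anomaly".

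The Outcome measurements text names detection of anomalies as primary, and health-related quality of life and cost-effectiveness as secondary, with patient and ultrasonographer perspectives in addition. Pregnancy outcome is not named there.

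**The concern.** A baseline characteristic is one fixed before allocation. In a randomised trial, a between-arm difference in such a variable is due to chance. A variable that arises after allocation is different, because a difference in it may be a consequence of the intervention. Putting pregnancy outcome on the baseline list gives it the wrong interpretation in both directions: a significant result would read as a chance imbalance, and a non-significant one as reassurance that the arms were comparable.

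This variable matters because the strategy under test brings detection forward to 11 to 14 weeks. How many pregnancies end in termination or fetal loss in each arm is something readers of the trial will want to know. The only between-arm analysis the article states for it is the one labelled baseline.

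**Working it through.** The plan states no figure on this point. The check is a comparison of sections, followed by an illustration on assumed rates.

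**1. Is it the study pregnancy or an earlier one?** The phrase stands next to parity, so the outcome of earlier pregnancies is a conceivable meaning. Table 1 speaks against it: the heading Pregnancy outcome is used only for the study pregnancy, and earlier pregnancies come under obstetrical history.

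**2. Is it known at randomisation?** No. Study population admits women up to 14 + 0 weeks and excludes non-viable pregnancies and anomalies found before randomisation. Live birth, termination or demise of the study pregnancy is settled later.

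**3. Could the intervention change it?** Plausibly. The Background counts the lower risk and less invasive methods of early termination among the advantages of early detection. The Discussion says earlier detection gives women "more time to consider continuation or termination of pregnancy". Neither passage predicts a difference in rates, but both link the first trimester scan to this decision.

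**4. Is it handled as an outcome elsewhere?** Not in the analysis text or in the named primary and secondary outcomes. Table 1 does list it for collection.

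**5. Illustration: could such a difference reach significance in the planned test?** Inputs: N = 2800 from the Sample size section; 1:1 allocation assumed, so n = 1400 per arm; two-sided 0.05 assumed; termination rates assumed, as the documents give none. With p̄ = (p1 + p2)/2,

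power = Φ{ [ |p1 − p2| − 1.96·√(2p̄(1 − p̄)/n) ] / √( [p1(1 − p1) + p2(1 − p2)]/n ) }

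For 2% v 4%: the null term is 1.96·√(2·0.03·0.97/1400) = 0.01264, and the standard error is √((0.0196 + 0.0384)/1400) = 0.00644. So (0.02 − 0.01264)/0.00644 = 1.14, and the power is 0.87.

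| Assumed rates | Chance of p < 0.05 |
|---|---|
| 2% v 3% | 40% |
| 2% v 3.5% | 68% |
| 3% v 5% | 77% |
| 2% v 4% | 87% |

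If rates differed by one or two percentage points, a significant result under the baseline label would be a realistic event. The table does not show that rates will differ.

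**6. What the right presentation would give.** With the same standard errors, an observed 2% v 4% would be a risk difference of 2.0 points (95% CI 2.0 ± 1.96·0.644, or 0.7 to 3.3). An observed 2% v 3% would be 1.0 point, with standard error √((0.0196 + 0.0291)/1400) = 0.0059 and 95% CI −0.2 to 2.2.

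**The case against.** The best defence is that this is a slip of wording. Table 1 classifies the variable correctly, the phrase is one item in a list of examples, and the article uses the word characteristics loosely: the title of Table 1 calls everything in it patient characteristics, outcomes included. The text says the variables will be compared, and does not say that a difference will be treated as imbalance. All of this is fair, and it limits the weight of the point. It does not remove it, because the analysis section is what an analyst follows, and there the variable is called baseline and is tested with the baseline set.

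Several stronger readings are tempting, and the document does not support them.

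- A reader might infer that results will be adjusted for pregnancy outcome. No adjusted model is stated.
- A reader might infer that the size of a difference would be hidden. Categorical data are to be shown as number and percentage, so the proportions in each arm would be visible. What is not provided for is their presentation as an effect, with an interval.
- A reader might infer that the protocol expects different termination rates, citing "Parents’ decision for continuation of the pregnancy is likely to be affected by this". That sentence follows one on what the second trimester scan shows, and that scan is usual care. The other statements bear mainly on time to decide and on how early a termination takes place.
- A reader might count the many uncorrected tests on true baseline variables as part of the same error. Such tests are uninformative after randomisation, but that is a separate matter of reporting practice. No decision is tied to them and they change no result.

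The article may also condense a fuller protocol or analysis plan. That would excuse missing detail, but not a variable stated to be baseline when it is not.

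**Conclusion.** The point holds as a misclassification. The Data-analysis section treats as baseline a variable that Table 1 shows to arise after randomisation and that the intervention could plausibly change. A real difference in terminations or fetal losses would be reported under the wrong label, and readers could take an effect of the strategy for chance.

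The size is modest. One variable is affected, the primary comparison of detection rates is not directly altered, and the sample size is untouched. The conclusion rests on reading pregnancy outcome as Table 1 defines it. It does not rest on the assumed rates in the illustration, nor on any expectation that rates will differ.

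**What to change.** In the Data-analysis section, remove pregnancy outcome from the examples of baseline characteristics and state that the baseline table is limited to variables fixed before randomisation. Add a sentence that termination and intra-uterine fetal demise are post-randomisation outcomes, reported by allocated arm under the intention-to-treat principle already stated, with the between-arm risk difference and 95% CI for each.

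The cost is about two sentences of wording. The data are already listed for collection in Table 1, and there is no added burden for participants and no effect on sample size.

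Optionally, the significance tests on true baseline variables could be dropped and those variables presented descriptively. This improves reporting and is not needed to correct the error.
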